## Abstract

**Background:**

Attention-deficit/hyperactivity disorder (ADHD) is a common neuro-psychiatric problem, affecting 7-9% of children. Pharmacological interventions are widely used with behavioral treatments in ADHD. Still, the origin of ADHD is unclear, limiting pharmacological effectiveness and making adverse effects common. The use of complementary and alternative medicine (CAM) has increased, especially for developmental and behavioral disorders, such as ADHD. CAM is used by 60-65% of parents of children with ADHD to relieve ADHD-associated symptoms and to avoid the side effects of conventional medication. Acupuncture has been widely used to treat patients with ADHD, but the available evidence of its effectiveness is insufficient. Our aim was to evaluate the effectiveness and safety of acupuncture in patients (both and each treatment naive and conventional therapy children) with ADHD (any subtype) compared to the waitlist control.

**Methods/Design:**

This study is a waitlist controlled open trial. We used a computer generated randomization scheme. This randomised, controlled trial had two parallel arms (acupuncture, and waitlist group). Each arm consisted of 40 participants. The acupuncture group received acupuncture treatment two times per week for a total of 12 sessions over 6 weeks. Post-treatment follow-up was performed 3 weeks later to complement the 12 acupuncture sessions. Participants in the waitlist group did not receive acupuncture treatments during the first six weeks but were only required to be assessed. After 6 weeks, the same treatments given to the acupuncture group were provided to the waitlist group. The primary outcome of this trial included differences in Korean version of ADHD-Rating Scale (K-ADHD-RS) before randomization, 3 weeks and 6 weeks after randomization, and 3 weeks after completing the treatment.

**Discussion:**

Subjective measurements, like K-ADHD-RS, are commonly used in ADHD. Although these measurements have adequate reliability and validity, lack of objective assessment in ADHD may lead to some disputes, like parental placebo effects. More objective measurements, like Computerized Neurocognitive function Test (CNT) in this study, are needed in ADHD trials. Furthermore, this trial will provide evidence for the effectiveness of acupuncture as a treatment for ADHD.

**Trial Registration:**

Clinical Research Information Service (CRiS) KCT0000019

## Background

Attention-deficit/hyperactivity disorder (ADHD) is a common problem, affecting 7-9% of children. The defining features of ADHD are inattention, hyperactivity, and impulsivity [1]. There is an abundance of literature dedicated to research for the treatment of ADHD) [2-6]. Most of these research have focused on pharmacological therapies with less emphasis on psychotherapy and psychosocial interventions [7-9] and even less in the area of complementary and alternative medicine (CAM) [10,11]. However, the origin of ADHD is unclear, which limits pharmacological effectiveness and makes adverse effects common.

The widespread use of stimulant medications for ADHD, such as methylphenidate (MPD) and dex-amphetamine, is thought to enhance short-term behavioral, academic, and social functioning [12]. However, concern about side-effects, such as tics, insomnia, and irritability, as well as questions about the long-term safety of these medicines and personal preference to avoid stimulants, has led many parents to seek alternative treatments for ADHD [13-15].

The use of CAM therapies has increased, especially for developmental and behavioral disorders such as ADHD [10,13,16-18]. Data from family practice physicians and internists show that acupuncture is one the most frequently recommended CAM therapies [19,20]. Approximately 60-65% of parents with children diagnosed with ADHD have used CAM therapies [10,16,17,21,22]. Acupuncture is a relatively simple, inexpensive, and safe treatment compared to other conventional interventions. Acupuncture has been widely used to lessen the severity of the core symptoms in patients with ADHD [23,24]. As a therapeutic intervention, acupuncture is also increasingly practiced in some Western countries [25,26]. However, existing evidence may not be rigorous enough for acupuncture to be recommended for routine use.

Acupuncture can change brain activity [27-35]. A brain hemodynamic study conducted in Japan reported that acupuncture significantly decreased activity in the dorsomedial prefrontal cortex (DMPFC) [29]. Hyperactivity in the DMPFC is associated with various psychiatric diseases with socio-emotional disturbances such as schizophrenia and ADHD. A fluorodeoxyglucose positron emission tomography combined computed tomography (FDG-PET/CT) study in Korea reported changes in brain glucose metabolism in specific brain areas following stimulation by acupuncture [32]. Collectively, these findings suggest that acupuncture might be effective to treat ADHD.

There are a large number of studies of the clinical efficacy of acupuncture in ADHD published globally, especially in China, but not all demonstrate a beneficial effect on ADHD [13,23,24,36].

### Objectives

The present study aimed to evaluate the effectiveness of acupuncture in patients with ADHD (any subtype) compared to waitlist control and to evaluate the safety of acupuncture in patients with ADHD (any subtype).

## Methods/Design

### Design

A 6-week, randomised, waitlist controlled trial of acupuncture for the treatment of ADHD in children/adolescents is being conducted at Kyung-Hee Oriental Medical center, Seoul, Korea. All screening appointments and study visits occur in the neuropsychiatry clinic for outpatients. This study was ethically approved by the Kyung-Hee Korean Medical Center Institutional Review Board, and was registered with the Clinical Research Information Service (CRiS) (KCT0000019) as a waitlist controlled, randomised clinical trial. This study had two parallel arms (acupuncture and waitlist group) with a 1:1 patient allocation ratio (40 participants per arm).

### Care providers

The providers went through 6 years of regular Korean medical college education and each was licensed a Korean Medical Doctor (KMD) degree. All the KMDs have undergone acupuncture safety education. These practitioners were chosen on the basis of their expertise in the field, their certified status and agreement to abide by the study protocols. Every practitioner is an apprentice doctor of "Department of Neuropsychiatry, College of Korean medicine, Kyung-Hee University" during this trial period.

### Participants

Parents were initially screened by phone, and their children were included in the study if the inclusion criteria were met. The inclusion criteria includes being between 7-18 years of age, having a diagnosis of ADHD (any subtype) according to Diagnostic and Statistical Manual of Mental Disorders (DSM-IV) criteria and having an informed verbal and written consent from parents and participants. It did not matter whichever intervention (pharmacological, psychosocial therapy, educational, or occupational therapy, as examples) was used, if there were not any change of ADHD treatments/symptoms for the past 2 weeks. Exclusion criteria are a diagnosis of a developmental disorder, past history of epilepsy, the presence of another neurotic disorder, pregnancy, and any changes in medications during the course of the study. During waitlist period, a CGI-I score ≥6, is a cue for the participant to stop waiting and to drop-out.

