### Randomization and treatment allocation

This study is designed as a waitlist controlled open trial. Eligible participants were randomly allocated to one of two groups: group A (acupuncture) and group W (waitlist). In each group, participants were stratified according to the pharmacologic intervention at the initiation of the study. A computer generated randomization scheme was used. The principal investigator generated the random allocation sequences without any notice to sub-investigators. Stratified randomization was performed as a separate randomization procedure within each of two subsets of participants (without pharmacologic intervention, 1-60; with pharmacologic intervention, D1-D40. Other treatments were not concerned.) by using block size "4". Each number and its randomised letter (A or W) were placed in an opaque envelope. Each envelope was numbered consecutively from 1-60 and D1-D40. As each parent called to have their child screened, they were allocated the next consecutive number once they were eligible, so that for each eligible participant, no. 1 was allocated to envelope no. 1, etc. The screener was unaware of the sequence of group allocation at the time of screening phase. Hence, allocation was concealed at the time of recruiting.

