### Protocol

Group A (acupuncture group) continued with their existing program and the acupuncture protocol was added to their regimen. Group W (waitlist group) continued with their existing program and the waitlist protocol was added to their regimen. The participants in group A attended a clinical facility for the first 6 weeks and received 12 treatments (two times per week) for approximately 20 minutes. During this first 6-week period, group W consisted of children who continued with their existing ADHD treatment regimen as prescribed by their pediatrician, clinical psychologist and/or medical doctor. Then, the participants in group W were scheduled for another 12 treatments over the next 6 weeks (same as group A, two times per week).

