### Analysis

Tests of potential differences across study groups on demographic and clinical history variables were performed by means of analysis of covariance (ANCOVA) for continuous measures and Pearson χ^2 ^for categorical variables. Every analysis conducted using the SPSS software (SPSS 12.0KO for Windows^©^), and performed among two randomised (acupuncture, and waitlist) groups and their stratified (treatment naive, and conventional therapy) sub-groups. The primary analysis will compare outcomes for each primary and secondary outcome measure among the groups to estimate treatment effect with 95% confidence interval (CI). An intention-to-treat (ITT) analysis will be undertaken of the 3-week and 6-week (respectively 9-week and 12-week) data from the K-ADHD-RS, due to some participants who commence the study but do not complete.

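### A medication change during the study is listed as an exclusion criterion, though it is generally known only after randomisation, and the article does not reconcile this with its intention-to-treat analysis

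*Protocol article*

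**What the plan says.** The Participants section contains two different rules on medication.

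- The first looks back from entry. Any existing intervention is acceptable "if there were not any change of ADHD treatments/symptoms for the past 2 weeks".
- The second sits in the list of exclusion criteria beside true baseline conditions, and that list ends with "pregnancy, and any changes in medications during the course of the study".

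On timing, the Randomization and treatment allocation section says of children screened that "they were allocated the next consecutive number once they were eligible". On blinding, the same section says "This study is designed as a waitlist controlled open trial". Under Protocol, both groups keep their existing programme; for the first six weeks, "group W consisted of children who continued with their existing ADHD treatment regimen as prescribed by their pediatrician".

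On the analysis population, the Analysis section says "An intention-to-treat (ITT) analysis will be undertaken of the 3-week and 6-week (respectively 9-week and 12-week) data from the K-ADHD-RS", and gives as the reason "due to some participants who commence the study but do not complete".

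No section says what happens to the follow-up or the data of a child whose medication changes after allocation.

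**The concern.** An eligibility criterion should be decidable before allocation, and this one is not. The two-week rule already deals with instability before entry, so the only work left for the item is to act on children who are already randomised.

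If it is applied as an exclusion, the children analysed are no longer the children randomised. The loss need not be random. Families and prescribers know the allocation, background treatment continues in both arms, and a medication change may follow the course of symptoms. A waiting child who does badly and a treated child who does well could both have their medication changed, for opposite reasons. Removing either would damage the comparability that randomisation provides, and the net direction cannot be predicted.

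Leaving the matter open has its own cost. In an open trial, whether such children count could be settled after outcomes are known.

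**Working it through.** **Step 1: the sections side by side.**

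- Participants: a medication change during the study is an exclusion criterion.
- Randomization and treatment allocation: a number is allocated once the child is eligible. A change during the study therefore generally comes after allocation.
- Analysis: ITT for the K-ADHD-RS, because some children start and do not finish.

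Two readings are possible. (a) The child is excluded from the study and its data. That is not an analysis of all randomised children. (b) The child stops participating, but the data remain in the ITT set. That is compatible with the Analysis section but is not written anywhere. The label of exclusion criterion favours (a); the stated reason for ITT leaves room for (b).

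**Step 2: the plan's own figure.** Inputs from Sample size justification: difference 7.04, SD 9.9, two-sided 5%, power 80%.

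n per group = 2 × (1.960 + 0.842)² × 9.9² / 7.04² = 2 × 7.849 × 98.01 / 49.56 = 31.04, rounded up to 32.

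Allowing for 20% dropout: 32 / 0.8 = 40 per group, 80 in total. Both stated figures reproduce. With 32 per group, power is 0.812 by the normal approximation and 0.800 by the t-test.

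**Step 3: illustration of bias.** The documents give no rate of medication change, so the fractions here are assumptions. Take a normal outcome with SD 9.9, remove the worst-scoring fraction q of one arm, and remove nobody from the other. That arm's mean moves by

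shift = 9.9 × φ(z) / (1 − q), where z is the (1 − q) quantile of the standard normal distribution.

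For q = 10% (4 of 40): z = 1.2816, φ(z) = 0.1755, and shift = 9.9 × 0.1755 / 0.9 = 1.93 points. As a share of the target, 1.93 / 7.04 = 27%.

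That assumes removal follows the outcome perfectly. If removal follows a variable correlated 0.5 with the outcome, the shift halves to 0.97 points, and 0.97 / 7.04 = 14%.

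Other fractions at correlation 1:

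| Fraction removed | Shift (points) | Share of 7.04 |
|---|---|---|
| 5% | 1.07 | 15% |
| 10% | 1.93 | 27% |
| 20% | 3.46 | 49% |

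Higher K-ADHD-RS scores are worse. Removing the worst children from the waitlist therefore makes the control group look better and works against acupuncture. Removing the worst children from the acupuncture group works in its favour.

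**Step 4: illustration of power.** If exclusions came on top of the planned 20% dropout, the numbers per arm (rounded down) and power by the normal approximation would be:

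| Further exclusion | n per arm | Power |
|---|---|---|
| none | 32 | 0.812 |
| 5% | 30 | 0.786 |
| 10% | 28 | 0.758 |
| 20% | 25 | 0.710 |

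**The case against.** The strongest reply is that no contradiction is written. The Participants section can be read as governing who continues, and the Analysis section as governing who is analysed. A child taken out for a medication change is one who started and did not complete, which is the very case for which ITT is invoked. This stands. A reader might infer that the plan discards these children's data and so flatly contradicts its ITT statement, but the text does not say so. What remains is an ambiguity on a point that decides who enters the randomised comparison.

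The illustration is also one-sided by construction. It assumes a rate, places all removals in one arm, and takes them from the extreme tail; the 27% needs perfect correlation. The waiting list protocol says the control group gets no additional ADHD treatment during the wait, which narrows the route by which waiting children would have medication raised. Waitlist children with a CGI-I score of 6 or more already leave under a separate rule, and they would largely be the same children. It is tempting to add the two effects together, but that would count much of the same loss twice.

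A reader might also infer that secondary outcomes will not be analysed by ITT, because the statement names only the K-ADHD-RS. A condensed article commonly leaves analysis sets for secondary outcomes to the full protocol or analysis plan, so that inference is not supported and forms no part of this point.

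**Conclusion.** The point holds as a defect of wording with consequences for the analysis population. A post-randomisation event is placed among the exclusion criteria, the two-week rule makes it unnecessary for eligibility, and nothing links it to the ITT statement. If applied literally, it would remove randomised children from an open trial on an event that may depend on arm and outcome.

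Neither the size nor the direction of any bias can be established from the documents. The range of about 1.0 to 1.9 points (14 to 27% of 7.04) rests on an assumed 10% removal from one arm only, SD 9.9 and correlation 0.5 to 1.0. It shows that a modest rate could matter, not that it will. Severity: should be fixed.

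**What to change.** Reconcile the Participants and Analysis sections as follows.

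1. Limit the exclusion criteria to facts known before randomisation. The existing two-week stability rule already serves this purpose for medication.
2. Treat a medication change after randomisation as a recorded event, with its date and reason.
3. State that week 3 and week 6 assessments continue to be collected where possible, and that these children are analysed in their randomised group in the ITT analysis.
4. Present an analysis without them as a sensitivity analysis only.

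This concerns follow-up and analysis. It says nothing on how medication, study treatment or waiting should be managed.

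The cost is small but not nil. The ITT estimate will include the effect of some medication changes. Recruitment was already under way when the article was written, so any child already removed may lack week 3 or week 6 data. The number of such children, by arm, should be reported.

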### Measures

DSM-IV ADHD diagnostic criteria [1,37] were used by the principal investigator to establish a diagnosis. Once randomised, participants were evaluated by the principal investigator during study visits at baseline and weeks 3 and 6 (or 3, 6, 9, and 12). The reliable and validated Korean version of the ADHD rating scale (K-ADHD-RS) [38] was used pre- and post-intervention as a primary outcome measure.

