### Primary outcome measures

The primary outcomes for the study were changes in ADHD symptoms from baseline to week 6 (or from week 6-12) as measured by the K-ADHD-RS [38]. The K-ADHD-RS is an 18-item standardized, valid, reliable instrument for the diagnosis and also a weekly assessment tool for checking the of treatment response among children and adolescents with ADHD [39]. Each item on the instrument describes one of the symptoms of ADHD rated on a 0-3 point Likert scale (0 = never or rarely, 1 = sometimes, 2 = often, and 3 = very often) [39]. The principal investigator administered the K-ADHD-RS to the parent at each study visit. Nationally representative norms are available for the scale and were used to determine eligibility [39].

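### The protocol gives opposite orders for randomisation and the baseline K-ADHD-RS, and never says which rating is the analysed baseline or when the envelope is opened

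*Protocol article*

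**What the plan says.** The Abstract (Methods/Design) describes the primary outcome as "differences in Korean version of ADHD-Rating Scale (K-ADHD-RS) before randomization, 3 weeks and 6 weeks after randomization", with a further rating after treatment. On that text the first rating precedes allocation.

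The Measures section says "Once randomised, participants were evaluated by the principal investigator during study visits at baseline and weeks 3 and 6". On that text allocation comes first and the baseline visit follows.

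Three other places bear on the order without settling it:

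- Primary outcome measures defines the outcome as change from baseline to week 6. It has the principal investigator administer the scale to the parent at each study visit, and says of the scale: "Nationally representative norms are available for the scale and were used to determine eligibility".
- Randomization and treatment allocation says "As each parent called to have their child screened, they were allocated the next consecutive number once they were eligible", and also "Each number and its randomised letter (A or W) were placed in an opaque envelope". The number therefore fixes the arm. This section calls the trial open, says the principal investigator generated the sequence, and says the screener did not know it during screening. It mentions neither the baseline rating nor the moment at which the envelope is opened.
- The Discussion concedes that the assessor of every measurement, who was also the screener, was not blinded.

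**The concern.** Both statements are current text about the same rating, and they cannot both describe what is done. This is not detail that a condensed article leaves to a fuller document, because the article states the order twice, in opposite ways.

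In an open waitlist trial, a baseline completed before allocation is the one K-ADHD-RS rating that the parent can give without knowing the arm. If it is taken after allocation, that protection is lost. A parent who has just learned that the child will wait, or will be treated, may describe symptoms differently, and so may a rater who knows the arm. Because the endpoint is a change from baseline, any arm-related shift in the baseline passes into the estimated effect point for point. The direction cannot be known in advance.

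**Working it through.** **1. Order of events, section by section**

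| Section | What it implies | Explicit? |
|---|---|---|
| Abstract | rating, then randomisation | yes |
| Measures | randomisation, then baseline visit | yes |
| Primary outcome measures | some rating before allocation, since norms decide eligibility | by inference |
| Randomization and treatment allocation | number given once the child is eligible; baseline rating not mentioned | silent on the rating |
| Design | screening appointments and study visits named as two kinds of contact | silent on the order |

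One explicit statement stands against another. The eligibility text supports the Abstract only if the eligibility rating is also the analysed baseline, and no section says so.

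**2. The plan's own sample size**

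Inputs from Sample size justification: difference 7.04, SD 9.9, two-sided 5%, power 80%, dropout 20%.

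n = 2 × (1.960 + 0.842)² × 9.9² / 7.04² = 31.04, rounded up to 32 per group. With dropout, 32 / 0.80 = 40 per arm, or 80 in total. The stated figures reproduce and do not depend on this point.

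**3. Illustration of what an arm-related baseline shift would do**

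Assumptions, none of them in the document: a shift b of 1, 2 or 3 points between the arms at baseline, no true effect, and 9.9 as the SD of the change score. The protocol does not say whether 9.9 refers to a score or to a change.

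SE = 9.9 × √(2/32) = 2.475

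Error = Φ(−1.96 + b/SE) + Φ(−1.96 − b/SE)

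- b = 1: b/SE = 0.404, error 6.9%
- b = 2: b/SE = 0.808, error 12.8%
- b = 3: b/SE = 1.212, error 22.8%

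These shifts are 14%, 28% and 43% of the 7.04-point target (1/7.04, 2/7.04, 3/7.04).

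**4. Sensitivity to the SD assumption and to baseline adjustment**

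Now take 9.9 as the SD of a single score, with an assumed correlation ρ of 0.3 to 0.7 between baseline and week 6.

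- Change score: SE = 9.9 × √(2(1−ρ)) × √(2/32), bias b. At ρ = 0.5 this equals the case in step 3.
- Baseline as covariate (ANCOVA): SE = 9.9 × √(1−ρ²) × √(2/32), bias ρb.

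| Assumed shift | Error, change score | Error, ANCOVA |
|---|---|---|
| 1 point | 6–8% | 5–7% |
| 2 points | 11–18% | 6–12% |
| 3 points | 18–35% | 7–22% |

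Adjustment carries only the fraction ρ of the shift into the estimate, so it softens the problem without removing it.

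**The case against.** The case on the other side has four parts.

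- **The Measures sentence is loose.** It can be read as listing the visits of children who were randomised, without fixing when the envelope was opened. That reading is possible. It is not what the words say, and the document offers nothing else that decides the matter.
- **Other text favours a rating before allocation.** The Abstract says so, norms were used for eligibility, and a number was given only to an eligible child. The screener is said to have been unaware of the sequence during screening, so a rating made then by that person would be protected. This stands as a reason for caution. It would close the point only if the screening rating were named as the baseline.
- **Unblinded assessment is already conceded.** The Discussion does concede it and offers CNT40 and FAIR as objective measures. But it does not settle the order or mention what the parent knows at baseline, and those tests are not the primary outcome.
- **The illustrated shifts have no source.** This is correct, and they are labelled as assumptions above.

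A reader might go further and infer from "As each parent called to have their child screened, they were allocated the next consecutive number once they were eligible" that allocation happened at the telephone call, that eligibility checks followed it, and that children later found ineligible could be removed by arm. The documents do not support this. The same sentence makes eligibility the condition for receiving a number, Participants describes the telephone screen only as an initial step, and Design says "All screening appointments and study visits occur in the neuropsychiatry clinic for outpatients". Nor does this section count as a second statement that randomisation precedes baseline, because it never mentions the baseline rating.

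**Conclusion.** The concern holds as a contradiction that must be reconciled. The Abstract and Measures give opposite orders for the baseline of the primary outcome, and no section says which rating is analysed or when the envelope is opened. It is not shown that any baseline was in fact rated with knowledge of the arm, only that following Measures would allow it.

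The size is conditional. Error rates of about 7%, 13% and 23% in place of 5% rest on assumed shifts of 1, 2 and 3 points and on 9.9 being the SD of change with 32 per group. They are smaller, but still above 5%, with baseline adjustment.

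Fixing the order fully protects the parent's report. It protects the rating less, because the principal investigator generated the sequence and also administers the scale. That is a separate weakness, which a change of order does not cure.

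**What to change.** Reconcile the Abstract, Measures, and Randomization and treatment allocation so that they give one order:

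1. State which K-ADHD-RS rating is the analysed baseline, and whether it is the rating used for eligibility.
2. State that this rating and the other baseline measures are completed and recorded before the next envelope is opened, and who opens it.
3. For any child whose baseline was taken after allocation, flag the record. Add a sensitivity analysis that uses the pre-allocation eligibility rating as baseline where there is one, or otherwise compares week-6 scores without baseline. The week-6 comparison avoids a distorted baseline but is still open to unblinded rating at week 6.
4. If such children exist, report this as a limitation.

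The cost is a few sentences of protocol text, a fixed sequence of steps within existing visits, one flag on the case record form and one extra analysis. No added visit or participant is needed. Recruitment and withdrawals describes recruitment as ongoing, so the order can still be fixed for children not yet enrolled.
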